**Figure 1. F0001:**
[figure not shown]
Procedure of inclusion. WDEQ-A: Wijma delivery expectations/experience questionnaire; PCL-5: PTSD checklist for DSM-5; FoC: fear of childbirth; PTSD: posttraumatic stress disorder.

### Intervention

4.3. 

Participants will be randomized to either EMDR therapy or CAU.

#### EMDR therapy group (fear of childbirth: *n* = 60; PTSD: *n* = 25)

4.3.1 

The EMDR therapy group will receive a maximum of three 90-min sessions, in addition to standard care during pregnancy. EMDR is a psychological intervention that has been developed for the treatment of traumatic memories (Oren & Solomon, 2012). It is internationally recognized as a first choice therapy for treating PTSD (NICE, 2005; WHO, 2013). EMDR therapy will be applied according to the Dutch translation of the standard EMDR protocol. The standardized procedure involves a combination of (1) focusing on the most distressing images of the traumatic event (or in case of FoC: worst-case scenario), including corresponding emotions, cognitions and physical response; and (2) repeated series of eye movements as a bilateral stimulation, followed by free associations. Current distress is rated until the distress level is (as close to) zero, after which a positive cognition is introduced corresponding to the image. The hypothesis is the traumatic event is unprocessed. By taxing patient’s working memory by both the image and eye movements simultaneously, the memory is reconsolidated less vividly. All therapy sessions will be videotaped. Tapes will be scored to determine treatment fidelity by using the EMDR Fidelity Scale (Korn, Zangwill, Lipke, & Smyth, 2001).

#### Care-as-usual group (fear of childbirth: *n* = 60; PTSD: n = 25)

4.3.2 

CAU is defined as standard care during pregnancy, with routine obstetrical checks. Assuming good clinical care, anxious pregnant women and those with traumatic childbirth experiences may receive more counselling compared to not-anxious pregnant women, but will (probably) not be referred for EMDR therapy. Type and frequency of any form of professional care will be registered.

### Procedure

4.4. 

Women with a gestational age between eight and 20 weeks, regardless of parity, who score above the cut-off score of the Wijma delivery expectations questionnaire (WDEQ-A) at time of screening will be invited for a clinical interview (see Figure 2). In case of multiparity, the PTSD checklist for DSM-5 (PCL-5) is administered at time of screening in addition.

**Figure 2. F0002:**
[figure not shown]
Study design.

During the clinical interview, traumatic events are explored in all women with the life events checklist (LEC-5). If appropriate, subsequently the clinician administered PTSD scale (CAPS) will be administered to diagnose PTSD (childbirth related, or not). In case of several traumatic events, the CAPS will be administered for each event separately. A pregnant woman is eligible for randomization for PTSD when a PTSD diagnosis can be obtained using the CAPS, with previous childbirth being the index trauma. PTSD with index trauma other than childbirth will be registered and analysed as co-existing psychiatric disorder. When informed consent is obtained, computer-assisted randomization will take place to allocate participants to either EMDR therapy or CAU. If the woman does not meet the criteria for PTSD after previous childbirth, but does score above cut-off on the WDEQ-A, she is eligible to be randomized for FoC (Figure 1). Measurements of (PTSD and/or FoC) symptoms take place between sessions (with childbirth being the index event of the PSS-SR questionnaire): at the start of each therapy session, or in case of CAU, measurements are done two, four and six weeks after randomization by email. Post-treatment antepartum measurement takes place at about 32–34 weeks of gestational age by a blinded assessor. If there is unblinding during the interview, another assessor will finish the interview. Final follow-up takes place two to three months after childbirth. Perinatal healthcare providers are semi-blinded: randomization results are not sent to the professionals, but if a pregnant woman would like to share information with her healthcare provider it is not prohibited.

A limitation for recruitment until 20 weeks of gestation has been chosen to ensure that there is enough time for planning an interview, arranging for therapy logistics, and for scheduling three therapy sessions before post-treatment sessions will take place around 32–34 weeks of gestation.

### Instruments

4.5. 

The order in which the instruments are administered can be seen in Table 1. The following instruments are used:

**Table 1. T0001:** Timing of instruments.

			In between sessions		t1		t2	
	Screening	t0	EMDR	CAU	EMDR	CAU	EMDR	CAU
Instruments								
*Clinical interview*								
CAPS(+LEC-5)	-	x*	-	-	x*	x *	-	-
MINI-plus	-	x	-	-	x	x	-	-
*Self-report questionnaires*								
PCL-5	x	-	-	-	-	-	-	-
PSS-SR*	-	x	x	x	x	x	x	x
HADS	-	x	-	-	x	x	x	x
Satisfaction scale	-	-	-	-	-	-	x	x
WDEQ								
version A	x	-	x	-	x	x	-	-
version B	-	-	-	-	-	-	x	x

CAPS: clinician-administered PTSD scale; CAU: care-as-usual; EMDR: eye movement desensitization and reprocessing therapy; HADS: hospital anxiety and depression scale; LEC-5: life events checklist; MINI-plus: mini international neuropsychiatric interview-plus; PCL-5: PTSD checklist for DSM-5; PSS-SR: PTSD symptom scale; PTSD: posttraumatic stress disorder; WDEQ-A/B: Wijma delivery expectations/experiences questionnaire

*Only if experienced a traumatic event.

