### Sample size

4.7. 

The main treatment outcomes of the current study are the effectiveness of EMDR therapy for treating PTSD and FoC. In practice, this corresponds to the difference in total CAPS or WDEQ scores between the EMDR and CAU group at follow-up during pregnancy. In both cases, a significance level of 0.05 and power of 80% is used. A one-sided significance level is chosen according with our hypothesis to find a reduction in PTSD or FoC symptoms. For PTSD, expecting a large effect size of at least 0.8 (Gerger et al., 2014), this results in 21 patients needed per group. The sample size was set at 25 patients each group, calculating for 20% patient attrition. For FoC, EMDR therapy effect size is not known yet. The most comparable data is EMDR therapy for dental phobia, which showed a large effect size (Doering et al., 2013). We estimated a medium effect size of 0.5, which results in 50 patients needed per group. With 20% patient attrition, this leads to a requirement of two groups of 60 patients for FoC.

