### Statistical analyses

4.8. 

Descriptive statistics will be used to evaluate demographic, clinical (obstetrical and psychological) baseline characteristics of both arms. All data will be analysed according to intention to treat analysis: the data of all randomized subjects will be analysed using the groups (treatment vs. CAU) as defined at randomization. In both conditions symptoms will be measured at regular intervals, in order to monitor treatment results over time. The treatment group and CAU group will be compared on all outcomes, which will be analysed with linear mixed models (LMM). Baseline scores will be included as covariates, time as a categorical variable, and treatment condition as a fixed effect. The intercept will be treated as a random effect. Furthermore, we will use Chi-squared tests and independent *t*-tests to compare both treatment conditions at different times (alpha level 0.05), or Fisher’s Exact test and Mann–Whitney U-test when appropriate. Effect sizes from change in symptoms between baseline and post-treatment antepartum, and post-treatment postpartum will be calculated with Cohen’s d. Safety is objectified by measuring worsening of FoC/PTSD symptoms, neonatal and obstetrical outcomes, dropout, and determining the presence of adverse events. However, our study is not powered upon these safety measures, therefore this outcome will be shown descriptively.

All analyses will be performed using SPSS version 22.0 (IBM Corp, 2013).

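### PSS-SR is the only PTSD measure after the study birth, but a footnote restricts it to women with an unspecified traumatic event, and its index birth at t2 is not named

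*Protocol article*

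**What the plan says.** Table 1 (section 4.5) places the PCL-5 at screening only and the CAPS at t0 and t1 only. The PSS-SR is marked at t0, between sessions, at t1 and at t2, so it is the only PTSD instrument after the study birth. The CAPS has asterisks in single cells. The PSS-SR has its asterisk on the row label, so the condition "Only if experienced a traumatic event" covers every PSS-SR time point, t2 included.

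Section 4.4 names the event to be rated in a parenthesis about the between-session measurements: "with childbirth being the index event of the PSS-SR questionnaire". It sets t2 as follows: "Final follow-up takes place two to three months after childbirth". On finding events it says: "During the clinical interview, traumatic events are explored in all women with the life events checklist (LEC-5". Table 1 marks the LEC-5 at t0 and t1, not at t2.

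Eligibility differs between the trials (section 4.4). The PTSD trial requires an earlier birth as the event behind the diagnosis: "A pregnant woman is eligible for randomization for PTSD when a PTSD diagnosis can be obtained using the CAPS, with previous childbirth being the index". For the FoC trial: "If the woman does not meet the criteria for PTSD after previous childbirth, but does score above cut-off on the WDEQ-A, she is eligible", whatever her parity.

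Section 4.8 promises an intention-to-treat analysis of all randomised women, lists worsening of FoC or PTSD symptoms among the safety measures (shown descriptively), and adds: "Effect sizes from change in symptoms between baseline and post-treatment antepartum, and post-treatment postpartum will be calculated". Section 4.7 defines the main comparison: "this corresponds to the difference in total CAPS or WDEQ scores between the EMDR and CAU group at follow-up during pregnancy".

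**The concern.** The schedule decides who has a postpartum PTSD score at all, and no later analysis plan can recover scores that were not collected. In the FoC trial a conditional instrument does not fit with analysing everyone randomised.

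The measure matters for safety. Section 1 cites a sixfold increased risk of PTSD after childbirth in women with FoC. Section 2.1 cites a non-randomised counselling study in which posttraumatic stress symptoms were more frequent in the counselled women (19% against 2%). New PTSD symptoms after the study birth are therefore something this trial has reason to look for in both arms.

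In the PTSD trial, every woman who reaches t2 has at least two births behind her. If the rated birth is left open, her t2 score may concern a different event from her t0 score.

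**Working it through.** **The plan's own figures.** None is given for the PSS-SR at t2. Section 4.7 sizes the t1 comparison (one-sided 0.05, power 80%). With n per group = 2(1.645 + 0.842)²/d², d = 0.8 gives 19.3, so 20, and d = 0.5 gives 49.5, so 50. The t-based values are 21 and 51. The stated 21 and 50 reproduce, and this point does not touch them.

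**What the footnote does in each trial**

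| | Event may include the study birth | Only events found by LEC-5 before the birth |
|---|---|---|
| PTSD trial | Excludes nobody: entry requires a traumatic childbirth | Excludes nobody |
| FoC trial, earlier trauma | Rated at t2 | Rated at t2 |
| FoC trial, no earlier trauma | Rated at t2 only if the study birth was traumatic | Never rated at t2 |

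The bottom row is the problem. On the left, inclusion depends on the birth experience, which section 3.2 expects EMDR to improve. On the right, the subset does not depend on the study birth, so this selection bias is absent, but a woman whose first trauma is the study birth has no PTSD score.

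**Which change score is affected.** For PTSD symptoms, the baseline-to-postpartum effect size can only come from the PSS-SR, because no other PTSD instrument is marked at both t0 and t2. In the PTSD trial the t0 score can refer only to an earlier birth. The t2 score could refer to that birth or to the study birth.

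**Illustration of the left-hand reading; all inputs are assumptions.** Let L be how traumatic the study birth was and Y the PSS-SR score, both standard normal under CAU with correlation ρ. EMDR lowers both by 0.5 SD. Take 43% traumatic births under CAU, the upper general figure in section 1.

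- Threshold: c = 0.176. Under EMDR the standardised threshold is 0.676, so 24.9% exceed it.
- Mean of Y above the threshold, CAU: ρ × 0.3928/0.43 = 0.913ρ.
- The same, EMDR: ρ × 0.3174/0.2494 − 0.5 = 1.273ρ − 0.5.
- Difference: −0.5 + 0.359ρ, that is −0.36, −0.28 and −0.21 SD for ρ = 0.4, 0.6 and 0.8.
- If EMDR improved only the birth experience and left Y unchanged, the difference would be +0.14, +0.22 and +0.29 SD, against EMDR.

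This is the extreme case in which no FoC woman has earlier trauma. Suppose a share q has it, stays in regardless, and has the same distribution of Y. The mean under CAU is then (1−q)(0.3928)ρ/[q + (1−q)(0.43)]. Under EMDR it is (1−q)(0.3174)ρ/[q + (1−q)(0.2494)] − 0.5.

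- q = 0.25: 0.515ρ against 0.545ρ − 0.5. The difference is −0.5 + 0.030ρ, or −0.48 SD at ρ = 0.6.
- q = 0.50: 0.275ρ against 0.254ρ − 0.5. The difference is −0.5 − 0.021ρ, or −0.51 SD at ρ = 0.6.
- q = 0.25 with 20% traumatic births under CAU (9.0% under EMDR; densities 0.2800 and 0.1622): 0.75 × 0.2800/0.40 = 0.525ρ against 0.75 × 0.1622/0.3174 = 0.383ρ, minus 0.5. The difference is −0.5 − 0.142ρ, or −0.59 SD at ρ = 0.6.

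So the bias can shrink the effect, nearly vanish or exaggerate the effect, depending on q and the event rate. The documents give neither for this population.

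**The case against.** The strongest reply is that selection after randomisation is not written anywhere. The only stated way of finding events is the LEC-5 at the t0 and t1 interviews, both before the birth, and no event screen is scheduled at t2. That stands: the reading tied to events before the birth has the better textual support, and under it the selection bias is absent. It does not rescue the schedule, because that reading leaves FoC women without earlier trauma unmeasured.

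A reader might infer that the footnote breaks the intention-to-treat comparison in both trials, that only women with a traumatic study birth would be rated, and that a real benefit would be hidden. The documents do not support this. Entry to the PTSD trial already satisfies the condition. FoC women with earlier trauma stay in on either reading. The direction of any bias is not fixed.

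It is also fair to say that little of the main result depends on this. The sized comparison is CAPS or WDEQ at t1. The FoC hypotheses in section 3.2 name no PTSD-symptom outcome. WDEQ-B, HADS and the satisfaction scale are given at t2 without condition. The safety display is unpowered and descriptive. This limits the weight of the point. Descriptive safety data still need to be collected from the women at risk.

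Finally, the index birth on the t2 form may be set out in the full protocol, which is not shown, and a change from baseline would most naturally keep the earlier birth. That is plausible, but the only text on the index event says just childbirth, and that is ambiguous once there are two.

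**Conclusion.** The point holds as a defect in a secondary and safety outcome. It rests on the position of the asterisk in Table 1 and on the absence of any other PTSD measure at t2.

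In the FoC trial, the postpartum PTSD-symptom comparison and the description of worsening are impaired on either reading: by selection on a post-randomisation outcome, or by missing new cases in women with no earlier trauma. In the PTSD trial, the only problem is the unnamed index birth in the baseline-to-postpartum effect size.

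No size can be derived from the documents. The range in the working, from a 0.50 SD benefit appearing as 0.21 SD to its appearing as 0.59 SD, is an illustration. It depends on the assumed event rates, correlations, equal treatment shifts and share with earlier trauma, and applies to only one of the two readings. The primary comparisons at t1 and their sample sizes are unaffected.

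**What to change.** - At t2, give the PSS-SR to every randomised woman in both trials, with the study birth as the named index event, and compare the arms in all randomised women.
- In the FoC trial, make this a comparison of t2 scores that does not require a baseline PSS-SR, because some women will have none. The two-group tests already listed in section 4.8 can serve.
- In the PTSD trial, also collect the PSS-SR at t2 for the earlier index birth, and use only that version for the baseline-to-postpartum effect size.
- Limit the footnote to the CAPS and the pre-birth PSS-SR, and state which events count there and at which interview this is determined.
- If the full protocol already settles these points, align Table 1 with it.

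The cost is small: a changed footnote, a named index birth, 17 further self-report items for FoC women who would otherwise be skipped, and a second set of 17 in the PTSD trial, all at an existing follow-up. Section 6 reports that recruitment is under way, so t2 assessments still to come can be changed. Any already done under the old rule should be identified in the report.

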#### PTSD checklist for DSM-5 (PCL-5) (Boeschoten, Bakker, Jongedijk, & Olff, 2014; Weathers et al., 2013)

4.5.1 

The PCL-5 is the DSM-5 version of the PCL. The PCL-5 is a 20-item self-report questionnaire assessing the 20 symptoms of PTSD according to DSM-5. Participants are asked to rate the severity of PTSD symptoms in the past month on a five-point scale from 0 (‘not at all’) to 4 (‘extremely’). Women meet the cut-off value when they report symptoms in accordance with the DSM-5 criteria: each item rated 2 (‘moderately’) or higher counts as a symptom, in addition at least one B item (questions 1–5), one C item (questions 6–7), two D items (questions 8–14) and two E items (questions 15–20) are required to meet the cut-off. Initial psychometric evaluation showed a strong internal consistency (0.94) (Blevins, Weathers, Davis, Witte, & Domino, 2015).

#### PTSD symptom scale (PSS-SR) (Foa, Cashman, Jaycox, & Perry, 1997)

4.5.2 

The PSS-SR is a 17-item self-report version of the semi-structured questionnaire to assess symptoms of PTSD in the past week. Items are scored on a four-point scale from 0 (‘not at all’/‘only one time’) to 3(‘almost always’/‘five or more times a week’). Psychometric properties are good, with internal consistency and test-retest reliability being 0.91 and 0.74, respectively (Foa et al., 1997).

#### Life events checklist (LEC-5) (Weathers et al., 2013)

4.5.3 

The LEC-5 is a self-report questionnaire to screen for potentially traumatic events during one’s life. Sixteen events which are known for their potential to cause PTSD, and one additional item for other extreme events are assessed. In our study it is used to identify the index traumatic event for administration of the CAPS-5.

#### Clinician-administered PTSD scale (CAPS-5) (Boeschoten et al., 2014)

4.5.4 

The CAPS-5 is the gold standard for diagnosing PTSD. It is a structured interview comprising 30 items including all 20 DSM-5 PTSD symptoms. Per item a severity rating is calculated by combining information about frequency and intensity. For DSM-5 PTSD diagnosis, a symptom is considered present when severity score is rated 2 (‘moderate’) or higher (range 0–4). Following DSM-5 criteria, one B, one C, two D and two E criteria are required. Research on the psychometric properties of the Dutch translation of CAPS-5 is currently being conducted, but the internal consistency of the Dutch CAPS-IV was good, ranging from 0.63 to 0.79 for clusters, to 0.89 overall (Hovens et al., 1994).

#### Mini international neuropsychiatric interview-plus (MINI-plus) (Sheehan et al., 1998)

4.5.5 

The MINI-plus is a structured interview for axis I DSM-IV conditions. In the current study, it is used to evaluate comorbidity, among which are mood disorders (i.e. major depressive episode, manic episode), anxiety disorders (i.e. panic disorder, specific phobia), substance abuse (alcohol, drugs), and psychotic disorders. Each chapter starts with one or more screening questions, and, if positive, is followed by further exploration before a specific diagnosis is made. There is a reasonable to good concurrent validity.

#### Hospital anxiety and depression scale (HADS) (Zigmond & Snaith, 1983)

4.5.6 

The HADS is a 14-item self-report questionnaire with a two-factor structure to measure anxiety and depressive symptoms. Each item is scored 0–3. Each subscale had a cut-off level of ≥8 for clinical significance. Internal consistency of the total scale and both subscales is found to be good (range 0.71–0.9) (Spinhoven et al., 1997).

#### Satisfaction scale

4.5.7 

Satisfaction around pregnancy and delivery is measured by the question ‘how satisfied are you about your pregnancy’, and ‘how satisfied are you about your delivery’ on a 10-point scale, where 0 equals extremely unsatisfied, and 10 extremely satisfied.

#### Wijma delivery expectations/experiences questionnaire (WDEQ-A/B) (Wijma, Wijma, & Zar, 1998)

4.5.8 

The WDEQ is a 33-item self-report questionnaire assessing FoC during pregnancy (version A), and after delivery (version B) in terms of the woman’s cognitive appraisal of childbirth. It was designed as a monofactorial scale, all 33 items being scored on a six-point scale leading to a sum score between 0 and 165, with higher score equalling more FoC. The WDEQ can be dichotomized to conclude if there is FoC or not (cut-off ≥85). Internal consistency is found to be high (≥0.87) (Wijma et al., 1998).

### Interrater reliability and treatment fidelity

4.6. 

All clinical interviewers receive an official training in assessment of the MINI and CAPS. Interrater reliability of assessment of the clinical interviews (MINI, CAPS) will be measured by scoring interviews by two independent assessors, or group wise scoring video tapes. Interrater reliability will be enhanced by supervision of each clinical interview.

All four therapists are psychologists with a postdoctoral degree in psychology. They are not part of the research team, and work at different sites. They have completed the basic and advanced EMDR training course accredited by the Dutch National EMDR Association (www.emdr.nl), and have at least one year experience with providing EMDR therapy. Patients will be randomly and equally distributed among therapists. All therapy sessions will be videotaped, and a selection will be rated for treatment fidelity. Group supervision every three to four months is obligatory for all therapists during the whole study duration. After each first session with a new patient, a case conceptualization will be emailed for supervision, including: the story of the traumatic event, with a hierarchy of the most relevant traumatic moments (targets) regarding to the current impairment. Deviations from protocol will be noted and reported.

The reliability of medical record data will be ascertained by double data entry of 20% of all records, and there is a build-in quality check in the data entry system.

### Sample size

4.7. 

The main treatment outcomes of the current study are the effectiveness of EMDR therapy for treating PTSD and FoC. In practice, this corresponds to the difference in total CAPS or WDEQ scores between the EMDR and CAU group at follow-up during pregnancy. In both cases, a significance level of 0.05 and power of 80% is used. A one-sided significance level is chosen according with our hypothesis to find a reduction in PTSD or FoC symptoms. For PTSD, expecting a large effect size of at least 0.8 (Gerger et al., 2014), this results in 21 patients needed per group. The sample size was set at 25 patients each group, calculating for 20% patient attrition. For FoC, EMDR therapy effect size is not known yet. The most comparable data is EMDR therapy for dental phobia, which showed a large effect size (Doering et al., 2013). We estimated a medium effect size of 0.5, which results in 50 patients needed per group. With 20% patient attrition, this leads to a requirement of two groups of 60 patients for FoC.

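### The 20% attrition allowance was evidently added as n × 1.2 instead of n ÷ 0.8, so neither trial keeps its own required number per group

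*Protocol article*

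**What the plan says.** Everything at issue stands in section 4.7 (Sample size) of the protocol article. For both trials "a significance level of 0.05 and power of 80% is used", and the test is one-sided: "A one-sided significance level is chosen according with our hypothesis".

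- **PTSD trial.** The authors plan by "expecting a large effect size of at least 0.8", and "this results in 21 patients needed per group". Enrolment follows: "The sample size was set at 25 patients each group, calculating for 20% patient attrition".
- **FoC trial.** "We estimated a medium effect size of 0.5, which results in 50 patients needed per group". Enrolment follows: "With 20% patient attrition, this leads to a requirement of two groups of 60 patients for FoC".

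The factor used to allow for attrition is not written out. Sections 4.3.1 and 4.3.2 repeat 25 and 60 per group, and the abstract gives the totals as 50 and 120.

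**The concern.** An attrition allowance should leave the required number after the losses. If a fraction *a* of those enrolled is lost, a required number *n* calls for *n* / (1 − *a*) enrolled. Adding *a* × *n* falls short, because the loss applies to the enlarged group and not to the original one. The pairs 21 to 25 and 50 to 60 look like the second calculation.

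If so, each trial drops below its own stated requirement at exactly the dropout it plans for, and readers would credit it with a safety margin that it does not have.

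**Working it through.** **Inputs** (section 4.7, with 1:1 allocation from section 4.2): one-sided α = 0.05; power 80%; standardised difference d = 0.8 (PTSD) and 0.5 (FoC); attrition 20%; enrolled 25 and 60 per group.

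**1. Reproducing the required numbers.**

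Normal approximation: n per group = 2(z₀.₉₅ + z₀.₈₀)² / d², with (1.645 + 0.842)² = 6.18.
- d = 0.8: 2 × 6.18 / 0.64 = 19.3, so 20
- d = 0.5: 2 × 6.18 / 0.25 = 49.5, so 50

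Exact two-sample t-test: the smallest n with power of at least 80%, from the noncentral t with 2n − 2 degrees of freedom and noncentrality d√(n/2).
- d = 0.8: n = 20 gives 79.94%, n = 21 gives 81.68%, so 21
- d = 0.5: n = 50 gives 79.89%, n = 51 gives 80.59%, so 51

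The stated 21 is the exact answer, and the stated 50 is the normal-approximation answer. Both reproduce to within one woman. Two-sided versions give 25 or 26 (PTSD) and 63 or 64 (FoC), so the one-sided setting is confirmed.

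**2. Reproducing the enrolled numbers.**

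| | PTSD | FoC |
|---|---|---|
| Required (stated) | 21 | 50 |
| × 1.2 | 25.2 | 60.0 |
| ÷ 0.8, rounded up | 26.25 → 27 | 62.5 → 63 |
| Enrolled (stated) | 25 | 60 |

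Multiplying by 1.2 gives the stated figures (25.2 rounded down, 60 exactly). Dividing the stated requirements by 0.8 does not. Reaching 25 and 60 by division would need starting values of 25 × 0.8 = 20 and 60 × 0.8 = 48, and the article states 21 and 50.

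**3. What remains after 20% attrition.**

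- PTSD: 25 × 0.8 = 20, one below 21
- FoC: 60 × 0.8 = 48, two below 50

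**4. Power with those numbers** (one-sided 0.05).

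| | Exact t | Normal approximation |
|---|---|---|
| PTSD, 20 per group, d = 0.8 | 79.9% | 81.2% |
| FoC, 48 per group, d = 0.5 | 78.4% | 79.0% |

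**5. Attrition that the enrolled numbers do cover.**

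- PTSD: 1 − 21/25 = 16.0%
- FoC: 1 − 50/60 = 16.7%, or 1 − 51/60 = 15.0% with the exact requirement of 51

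Full cover for 20% would take 27 and 63 per group (54 and 126 in total, against 50 and 120). With 51 as the FoC requirement it would take 51 / 0.8 = 63.75, so 64 per group.

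**The case against.** The case on the other side is that the slip hardly matters.

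- **PTSD power.** It is 79.94% at 20 per group, which rounds to the stated 80%. This stands: in that trial the stated count of 21 is missed, but the power is practically kept.
- **FoC power.** The loss is 1.0 to 1.6 points, far less than the uncertainty about an effect size that section 4.7 itself says is unknown. This also stands, as a statement about size.
- **Baseline adjustment.** Section 4.8 plans a mixed model with baseline scores as covariates, analysed by intention to treat. The article gives no baseline-to-outcome correlation. If one assumes 0.2, FoC power with 48 per group is 79.9%; 0.25 gives 80.7% and 0.3 gives 81.7%. For PTSD with 20 per group, 0.1 already gives 80.3%. Women who leave early but have an intermediate measurement may also contribute. So the real loss may be nil. But section 4.7 claims no such gain: it sizes the trials on a standardised difference in follow-up scores and adds women expressly because of dropout.
- **Inference.** The factor 1.2 and the two sizing methods are inferred, since the article names neither a factor nor a formula. That is fair, and 50 against 51 is close to rounding. The main point needs neither inference: 20 is less than 21 and 48 is less than 50 whatever formula was used.

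**Conclusion.** The concern holds. The required number, the attrition rate and the enrolled number in section 4.7 cannot all be right together, in either trial. At the planned 20% attrition, PTSD ends one woman per group short and FoC two. Power is about 0.1 point below 80% in PTSD and 1.6 points below in FoC.

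These figures assume an unadjusted two-sample t-test on the women who remain, one-sided 0.05, and effects of 0.8 and 0.5. The planned covariate adjustment could recover the loss, but the sample-size statement does not draw on it.

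This is a small arithmetic error in a figure the trials rely on, larger in FoC than in PTSD. It does not threaten the design. The 50-against-51 difference is secondary.

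**What to change.** Leave enrolment at 25 and 60 per group and correct the statement in section 4.7 in one of two ways:

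- **State the attrition covered:** 16% for PTSD; for FoC, 15% with a requirement of 51, or 16.7% if 50 is kept.
- **Keep 20% attrition and state the power:** 79.9% for PTSD and 78.4% for FoC, by t-test at one-sided 0.05.

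In either case name the method and use the same one for both trials. With the exact t-test, the FoC requirement reads 51.

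The cost is a sentence or two of text. Recruitment targets, procedures and the analysis do not change, and no extra patients are needed.
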